**Shipping Address:**

LAB 205, UCL Cancer Institute

[name]

[name]

[name]

- Once received at the laboratory, the samples will be stored in a secure location in -80 freezers. The temperature will be monitored using T-scan software and the freezers will have a CO2 back up system attached.
- When required, the aliquots will be sent to consortium partners for analyses in line with study SOP’s and MTA’s.

## Urine sample collection

- Urine samples will be collected by trial employed clinical trial practitioner in advance or on the day a MRI guided biopsy is taken. This could be in a dedicated clinic or on the ward but will always occur in advance of the biopsy.
- Urine samples will be provided by participants into urine collection bottles and processed according to ReIMAGINE Prostate Cancer Risk Lab manual.
- The samples will be logged into the FreezerPro database and stored temporarily at the collection sites.
- At the regular intervals the samples will be shipped using a courier to:

**Shipping Address:**

LAB 205, UCL Cancer Institute

[name]

[name]

[name]

- Once received at the laboratory, the samples will be stored in a secure location in -80 freezers. The temperature will be monitored using T-scan software and the freezers will have CO2 back up system attached.
- When required the aliquots will be sent to consortium partners for analyses in line with study SOP’s and MTA’s.

## Prostate tissue Collection

- In addition to diagnostic tissue collected for FFPE processing, up to 3 cores of fresh tissue (standard prostate biopsy cores) will be collected and frozen intraoperatively. For detailed information on preparation, storage and shipment of tissue samples please refer to the ReIMAGINE Prostate Cancer Risk Laboratory Manual.
- Once the samples are collected, they will be logged into FreezerPro and temporarily stored at the hospital sites at -80.

The samples will be shipped a regular intervals using courier to:

**Shipping Address**

LAB 205, UCL Cancer Institute

[name]

[name]

[name]

- Once received at the laboratory, the samples will be stored in a secure location in -80 freezers. The temperature will be monitored using T-scan software and the freezers will have CO2 back up system attached.
- When required tissue samples will be sent to consortium partners for analyses in line with study SOP’s and MTA’s.

## Paraffin and H&E slide collection

In addition to the samples collected at visit 1, all sites will send H&E slides and FFPE tissue blocks to Professor [name]’s laboratory (facilitated by the ReIMAGINE clinical trial practitioners).

H & E slides will be anonymised, scanned using high resolution scanners and uploaded to the ReIMAGINE image warehouse. Scanned H&Es could be subjected to additional central pathology assessment and morphological features captured using computer-based algorithm to identify H&E based biomarkers for improved patient risk stratification. Scanned H&Es could also be shared with partners to integrate with analyses of scans and molecular biomarkers.

A tissue technician will also acquire slices from the requested FFPE tissue blocks in line with the study SOP. The acquired slices will be stored in the [name] laboratory and transported in batches to consortium partners for analyses in line with study SOP’s and MTA’s. Additional sections will be subjected to molecular analyses, including genomic, mRNA expression and protein studies by the RE-IMAGINE consortium academic and industry partners.

Both H&E slides and FFPE tissue blocks will be returned to the relevant NHS pathology department.

Instructions on postage and packing will be shared with sites at SIV.

## Imaging databank

Clinical trial practitioners will request pseudonymised DICOM (Digital Imaging and Communications in Medicine) images from the standard of care prostate MRI each recruited participant had before entry to the study. These anonymised images will be uploaded to the CRUK funded National Cancer Imaging Translational Accelerator (NCITA) image repository, hosted by UCL.

A copy of these pseudonymised images will be transferred via the XNAT platform to the ReIMAGINE data warehouse hosted by Philips in the EU. Both platforms have strict safeguards against unauthorised access with established security procedures.

# PEER AND REGULATORY REVIEW

The study has been peer reviewed in accordance with the requirements outlined by UCL/UCLH.

The Sponsor considers the procedure for obtaining funding from the Medical Research Council to be of sufficient rigour and independence to be considered an adequate peer review.

The study was deemed to require regulatory approval from the Regional Ethics Committee and Health Research Authority. Each approval will be obtained before the study commences.

# ASSESMENT AND MANAGEMENT OF RISK

The table below summarise the risks and mitigations of all test above standard of care that are being performed:

| **Intervention** | **Potential risk** | **Risk Management** |
| --- | --- | --- |
| Tissue donation | Biopsies will be performed as part of standard of care, additional cores will be performed for research. A biopsy may result in bleeding, bruising and infection. | Performed by trained urologists, following trust standard operational procedures.  Maximum of 3 cores taken which should infer minimal burden. |
| Blood donation | Bruising, Pain, Bleeding and Infection | Performed by a trained phlebotomist, following trust standard operating procedures.  Or can be taken when cannula already in situ in preparation for prostate biopsy to avoid necessity for additional skin puncture. |
| Urine donation | None | Will be performed by the participant. |

# RECORDING AND REPORTING OF EVENTS AND INCIDENTS

This study is not expected to have any unexpected adverse events as the procedures that patients will receive form part of standard of care. Cross-sectional blood, urine and tissue samples will be collected at which point active follow-up to this component will end. Expected adverse events that occur thereafter may be due to the standard of care biopsy that is performed at the point the cross-sectional component ends.

Thus, this study will not document adverse events in particular however; any events that do occur should be recorded in the patient’s medical notes and will be reviewed during monitoring visits.

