Recruiting sites will register fully eligible and consenting patients using a software system (Research Data Collection Service - REDCap) hosted securely by UCL and Phillips (pseudonymised data only). After providing full informed consent, each patient will receive a unique patient ID. An additional separate REDCap database will be hosted securely by University College London (only) to handle identifiable data used for healthcare data linkage purposes.

Following consent, participants will be registered and screened against inclusion/exclusion criteria to confirm eligibility prior to registration (see section 7). Any participant who meets all the inclusion criteria and none of the exclusion criteria will be offered to continue with the study and will be registered. They will attend a baseline visit in order to start collecting baseline measurements.

Eligible men will be invited to consent to the following:

- Agreement to have blood and urine taken for biomarker assessment.
- Agreement for up to 3 additional prostate biopsy cores to be taken at the time of their standard of care diagnostic prostate biopsy.
- Agreement to share standard of care paraffin processed tumour blocks and H&E slides for additional research analysis. These will be returned to NHS sites.
- Donation of anonymised imaging files / data from their baseline MRI scan.
- Agreement to healthcare data linkage through NHS Digital, Public Health England and/or other relevant bodies.

Any patient who provides full informed consent to the study but does not fulfil all other eligibility criteria will be recorded as a screen failure. These screen failure patients will not receive a unique patient ID number.

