***Demographic and general measurements***

- Medical history
- Demographics
- Family History
- Ethnicity
- Age
- Co-Morbidities
- Medication use

All consented patients who are deemed eligible will have already been advised and/or have a scheduled visit for a prostate biopsy on clinical grounds as standard care. On the day of consent or at the time of the scheduled prostate biopsy participants will have the below interventions:

- Donation of blood will be drawn from men, either via a trained phlebotomist or from the cannula already in situ in preparation for their prostate biopsy.
- Donation of urine. Provided by participant in advance of prostate biopsy.
- Up to three additional biopsy cores will be taken at the time of the standard of care biopsy. Two cores will be taken from the radiologically guided area of suspicion and one control sample from the contralateral non-suspicious area.

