**Long term healthcare data linkage**

The study will obtain informed consent from participants to collect long term healthcare information from national records, such as the Office for National Statistics, NHS Digital, Public Health England, and/or other applicable NHS information systems, or national databases. No further visits will be required for this activity, but permission will be obtained to receive and hold this information. The research team will collect this healthcare information up to three years after last patient last visit (LPLV) and further funding will be sought to collect this longer term (until death time point should funding be successful).

**Figure 2:** ReIMAGINE Prostate Cancer Risk Trial Flow Diagram

*
[figure not shown]
*

** Blood and Urine collection will always occur before the prostate biopsy is performed but may not always be on the same day as the biopsy procedure.*

**Table 1:** Schedule of Assessments

| **Visit** | **Screening & Registration** | **Visit 1*** | **Non-Visit** | **In direct collection** |
| --- | --- | --- | --- | --- |
| Timing of Visit | Day -1 | Day 1 | 3-6 Weeks | n/a |
| Registration | X |  |  |  |
| Medical History | X |  |  |  |
| Eligibility confirmation | X | X |  |  |
| Informed Consent |  | X |  |  |
| PSA | X |  |  |  |
| Research Blood |  | X |  |  |
| Research urine |  | X |  |  |
| Targeted biopsy |  | X |  |  |
| Biopsy results |  |  | X |  |
| FFPE tissue block and H&E slide collection |  |  | X |  |
| Adverse Events review |  | X |  |  |
| Concomitant Medication review (if applicable) | X |  |  |  |
| Healthcare data linkage |  |  |  | X |

** Blood and Urine collection will always occur before the prostate biopsy is performed but may not always be on the same day as the biopsy procedure.*

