## Recording adverse events

All adverse events will be recorded in the medical records in the first instance.

As an observational trial this study involves no specific interventions and all participants will undergo standard of care investigations, although additional biopsies and a blood draw is required. No risk is expected from giving a urine sample.

A list of expected AEs which do not need reporting except for in the medical notes include the following. Severity can escalate to serious:

- Pain
- Blood in the urine
- Blood in the semen
- Blood in the stool or back passage
- Erectile dysfunction
- Urinary incontinence
- Urinary tract infection
- Fevers

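### Section 16 plans no study-level adverse event record on the ground that procedures are standard of care, yet research cores and a blood draw are added and serious events from them have no reporting route

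*Protocol*

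**What the plan says.** Section 5.1 asks men to consent to extra tissue sampling: "Agreement for up to 3 additional prostate biopsy cores to be taken at the time of their standard of care diagnostic prostate biopsy". The Visit 1 text repeats it: "Up to three additional biopsy cores will be taken at the time of the standard of care biopsy".

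Section 15 introduces its table as covering the "risks and mitigations of all test above standard of care that are being performed". The table includes tissue, blood and urine donation. For tissue it states that "additional cores will be performed for research. A biopsy may result in bleeding, bruising and infection". For blood it names bruising, pain, bleeding and infection.

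Section 16 expects no unexpected adverse events, "as the procedures that patients will receive form part of standard of care". It links later expected events to the standard of care biopsy alone and concludes: "Thus, this study will not document adverse events in particular". The sentence then continues: events that do occur go into the medical notes and are looked at during monitoring visits.

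Section 16.1 also places all adverse events in the medical records first, and it acknowledges that extra biopsies and a blood draw are needed. It adds: "A list of expected AEs which do not need reporting except for in the medical notes include the following. Severity can escalate to serious". Eight items follow. Section 16.2 excludes treatment-related serious events from collection and sends deaths to a death form.

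Table 1 and Appendix II both contain a row "Adverse Events review", marked at Visit 1 (Day 1) only.

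**The concern.** The decision to keep no study-level adverse event record rests on a premise that the preceding section and the following subsection both contradict. The diagnostic biopsy is routine care. The research cores and the research blood draw are not: they happen only because the man joined the study, so the study is answerable for what follows from them.

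Three things are at stake. A serious event after a research procedure has no stated path to the sponsor. The risk table's statement that the burden of the extra cores is minimal cannot be checked against any study count. And Section 6 provides for updating the information sheet when new safety information appears, but no study-level source would generate that information.

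**Working it through.** No power or sample size figure is involved, so the check is a comparison of the sections. The only arithmetic is an upper bound on exposure.

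1. **Exposure.** Up to 3 research cores per man (Section 5.1) and 1,000 men biopsied (Sections 4 and 9) give at most 3 × 1,000 = 3,000 research cores. Section 2 gives a cohort of 1,688 men; on that figure the bound is 3 × 1,688 = 5,064. Either number bounds needle passes. Neither is an estimate of harm.

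2. **Premise.** Section 16 describes the procedures as standard of care without exception. Section 15 places tissue and blood donation above standard of care, and Section 16.1 concedes the extras. Section 16 names only the standard of care biopsy as a source of later events, although the research cores are taken in the same session. The reason given for having no study-level documentation therefore fails on the protocol's own description.

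3. **Where events go.** Medical notes, then monitoring visits (Sections 16 and 16.1). No eCRF item, dataset or tabulation is mentioned.

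4. **Serious events.** Section 16.1 releases the listed expected events from reporting beyond the notes even if they become serious, which implies that other events are reportable. Section 16.2, whose title promises a procedure, covers only treatment-related events and deaths. A research core or blood draw is not a treatment, so a serious event from either is neither excluded nor given a route. The list also differs from the risk table: bruising is absent, and infection appears only as urinary tract infection and, indirectly, fevers.

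5. **Schedule.** The adverse event review falls at Visit 1, the same visit as the biopsy. Neither schedule says what the review records or where. A same-visit review cannot pick up events that begin later.

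6. **Follow-up window.** Section 16 ends active follow-up for the cross-sectional component once samples are collected. Section 5.3 continues collecting from medical records for 4-8 weeks. Table 1 puts the non-visit step, with the biopsy result, at 3-6 weeks. The three statements differ, but the last two show that a look at the records after the biopsy is already planned.

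**The case against.** The strongest reply is that notes-based, monitored recording is a deliberate and proportionate choice for an observational cohort. No primary or secondary outcome uses adverse event data. The extra cores are ordinary biopsy cores taken in the same procedure, so they plausibly add no new kind of event, and Section 16's premise is about unexpected events. Oversight also exists: events are reviewed at monitoring, Section 19 has the Chief Investigator take monitoring concerns to the sponsor, Section 18 sends incidents to the Trust, and a separate monitoring plan is to be written.

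Much of this stands, and it rules out several stronger readings that a reader might infer:

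- That the study records no adverse events. It does not say so; the sentence quoted from Section 16 goes on to require entry in the notes.
- That the sections cannot all be followed. A site could review events at Visit 1, write them in the notes and have them monitored.
- That a number of men harmed by the research cores can be given. The documents state no complication rate, and any assumed rate would cover the diagnostic cores too.
- That better recording would isolate research-core harm. In a single-arm cohort with one shared procedure, it would not.

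What the reply does not remove is the mistaken rationale, the missing route for serious events from research procedures, the undefined Day 1 review and the differing follow-up windows. Trust incident reporting does not reach the sponsor by itself, and Section 19 depends on someone first forming a concern.

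**Conclusion.** The point holds as an inconsistency in the protocol with a modest oversight gap behind it. The stated reason for keeping no study-level adverse event record conflicts with Sections 15 and 16.1 and sits badly with the scheduled review. Serious events from the research procedures have no stated route.

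The exposure is up to three research cores per man, at most 3,000 on the Section 9 target. The size of any harm is unknown and cannot be derived from the protocol. No planned outcome analysis is biased. The conclusion assumes that the monitoring plan and laboratory manual, which are not shown, do not already set up an eCRF record of these events. Even if they did, the text of Section 16 would still need correcting.

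**What to change.** Reconcile Sections 5.3, 15, 16, 16.1 and 16.2 with Table 1 and Appendix II:

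- Correct the standard-of-care rationale in Section 16 so that it acknowledges the research cores and blood draw.
- State in Section 16.2 how a serious event possibly related to either one reaches the sponsor.
- Say what the Day 1 adverse event review produces, and align the statements on when active follow-up ends.
- At the post-biopsy record review already planned (3-6 weeks in Table 1, 4-8 weeks in Section 5.3), enter on the eCRF any serious biopsy-related event and the number of research cores taken. Tissue samples are logged in FreezerPro under Section 13.3, which offers a cross-check on the core count.
- Report the result as a descriptive count, with no attribution to the research cores. It need not go to the 12-month review, whose remit in Section 4 is accrual, cancer incidence and the recruitment target.

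The cost is a protocol wording change, a short eCRF item and slightly more abstraction work. No new visit or procedure is needed. Events treated at another hospital may be missed, so the count would be a minimum.

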## Recording adverse events

All adverse events will be recorded in the medical records in the first instance.

As an observational trial this study involves no specific interventions and all participants will undergo standard of care investigations, although additional biopsies and a blood draw is required. No risk is expected from giving a urine sample.

A list of expected AEs which do not need reporting except for in the medical notes include the following. Severity can escalate to serious:

- Pain
- Blood in the urine
- Blood in the semen
- Blood in the stool or back passage
- Erectile dysfunction
- Urinary incontinence
- Urinary tract infection
- Fevers

## Procedures for recording and reporting Serious Adverse Events

As ReIMAGINE Prostate Cancer Risk is not an interventional study, no SAEs related to the treatment of prostate cancer or any other treatment related SAEs will be collected. These events must continue to be recorded in the participant’s medical records.

Death is a study primary end point, therefore deaths must be reported on a death form, and not as an SAE.

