## Primary Outcome

### **Cross sectional component primary outcome**

Presence of clinically significant prostate cancer confirmed on biopsy, defined as any Gleason pattern 7 or greater.

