### Longitudinal Component primary outcome

Time to metastasis and/or prostate cancer related death.

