## Secondary Outcomes

- Time to new prostate cancer in men without cancer at baseline
- Time to cancer progression* in men identified with prostate cancer at baseline
- Time to prostate cancer specific death and all-cause death in all men.

** Need for salvage therapy to the prostate following the primary treatment strategy, or, need for systemic therapy for prostate cancer treatment following failure of the primary treatment strategy.*

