# STUDY DESIGN

ReIMAGINE Prostate Cancer Risk is a multi-centre, prospective, observational, longitudinal cohort study of men referred to secondary care with a suspicion of prostate cancer or men who are undergoing further tests for prostate cancer staging assessment. Men with a serum PSA level of 20ng/ml or less, whose mpMRI scan has been scored as PIRADS/LIKERT score 3, 4 or 5, and who have been advised and accepted the need for a targeted and systematic prostate biopsy will be invited to enrol.

Men will be recruited across a number of high-volume NHS centres which already have an mpMRI based diagnostic pathway. The study has an initial cross-sectional component where consenting men will be asked to donate blood, urine, imaging files and prostate biopsy tissue for biomarker analysis before or at the time of their standard of care prostate biopsy.

After collection of the cross-sectional biological samples within ReIMAGINE, men will revert to NHS standard of care, attending a routine outpatient appointment for the results of their prostate biopsy outside of the trial setting. Although there are no further planned study visits all men will be consented for healthcare data linkage to measure long-term outcomes including cancer progression, development of metastases and mortality for the longitudinal component of the study.

The ReIMAGINE team aim to recruit 1,000 men with a PIRADs/LIKERT score 3, 4 or 5 who are undergoing an MRI-directed prostate biopsy. Of these 1,000 biopsies, we anticipate that 60% will have any cancer detected on histology (3+3 or greater) giving approximately 400 cases of clinically significant cancer (Gleason 7 or more).

After 12 months of accrual to the study an interim review will be performed by the ReIMAGINE scientific advisory board *(see appendix I for SAB membership)* who will review both accrual rates and cancer incidence with the remit of reviewing and advising on the final recruitment target.

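### Section 16.2 keeps every death out of SAE reporting because death is called a primary end point, but only prostate cancer related death is primary, and no study-level relatedness assessment is defined for other deaths

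*Protocol*

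**What the plan says.** Protocol section 16.2 sets the rule for deaths: "Death is a study primary end point, therefore deaths must be reported on a death form, and not as an SAE". It has no limit by cause or by time since biopsy, and it gives the death form no recipient, timeline or causality judgement.

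The outcome definitions are these:

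- Section 3.1.1, cross-sectional primary outcome: "Presence of clinically significant prostate cancer confirmed on biopsy, defined as any Gleason pattern 7 or greater".
- Section 3.1.2, longitudinal primary outcome: "Time to metastasis and/or prostate cancer related death".
- Section 3.2, among the secondary outcomes: "Time to prostate cancer specific death and all-cause death in all men".

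On research procedures, section 5.1 (Visit 1) states: "Up to three additional biopsy cores will be taken at the time of the standard of care biopsy". Section 15, which covers tests above standard of care, says of tissue donation that "additional cores will be performed for research. A biopsy may result in bleeding, bruising and infection". It also lists bruising, pain, bleeding and infection for the blood donation.

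**The concern.** Keeping endpoint deaths out of SAE reporting is a recognised arrangement, but it has to rest on the endpoint as defined. Here the reason given covers one group of deaths and the rule covers all of them.

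The group left over matters because the study adds procedures of its own. A man who dies of infection or bleeding after a biopsy session that included research cores has not reached a primary outcome. Under section 16.2 his death is still recorded only as an outcome. A site following the text would not be asked whether the research cores or blood draw might have contributed, and the CI and sponsor would have no defined prompt to consider it.

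**Working it through.** No power, sample size or event figure in the plan bears on this, so the check sets the sections side by side.

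**Step 1. Does the stated reason match the outcomes?**

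| Death | Primary outcome? | Secondary outcome? | Exempted by 16.2? | Covered by the reason given? |
| --- | --- | --- | --- | --- |
| Prostate cancer related | Yes (3.1.2) | Yes (3.2) | Yes | Yes |
| Any other cause, unrelated to study procedures | No | Yes, as all-cause death (3.2) | Yes | No |
| Possibly related to research cores or blood draw | No | Yes, as all-cause death (3.2) | Yes | No |

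The cross-sectional primary outcome (3.1.1) has no death component, so it cannot supply the reason. The exemption applies to all three rows and its reason to the first only.

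**Step 2. Is there a research procedure to which a death could be related?** Yes. Section 5.1 adds up to three cores and a blood donation. Section 15 treats both as additional to standard of care and names bleeding and infection among the risks. Section 16.1 acknowledges the extra biopsies and the blood draw, although the opening of section 16 reasons as if all procedures were standard care.

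**Step 3. Does another route supply a study-level notification and a relatedness judgement?**

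- *Death form (16.2).* Required, but no recipient, timeline or relatedness statement is given.
- *Notes reviewed at monitoring visits (16).* This is retrospective. The monitoring activities that section 19 names are protocol adherence, consent procedures and data quality; causality is not among them.
- *Adverse event review (Table 1 and Appendix II).* Scheduled at Visit 1 only, so a death in the following weeks would not be seen there.
- *DATIX (18).* Unexpected harm is reported to the Trust. No onward notice to the CI or sponsor is stated.
- *Immediate notice to CI and sponsor (17).* This is for protocol violations. A fatal complication of a correctly performed biopsy is not a breach.

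None of the five supplies both elements for a death possibly related to a research procedure.

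**Step 4. How many extra reports would a correction bring?** The documents give no mortality rate. As an assumption, take 0.5% to 2% a year from all causes, the 1,000 men of sections 4 and 9, and the 4-8 week record follow-up of section 5.3 (28 to 56 days):

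- lower end: 1,000 × (28 / 365.25) × 0.005 = 0.4 deaths;
- upper end: 1,000 × (56 / 365.25) × 0.02 = 3.1 deaths.

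This bounds the reporting load for deaths. It does not estimate procedure-related deaths, for which the documents give no basis.

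**The case against.** The strongest reply is that the mismatch is one loose sentence and that deaths are not ignored. A death must go on a study form, notes are reviewed at monitoring, and unexpected harm goes to the Trust. A study-specific monitoring plan is promised in section 19 but not shown, and the death form, also not shown, may already record cause or relatedness. The biopsy itself is standard care, so the research adds only a few cores and a blood draw.

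Much of this stands, and it rules out three stronger readings that a reader might infer.

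- *That a death from a research core escapes all safety review.* The routes just listed exist. What is missing is a defined study-level notification with a relatedness judgement.
- *That death is singled out.* It is not. Section 16 says the study will not specifically document adverse events, section 16.1 sends expected events to the notes even though they may become serious, and section 16.2 does not collect treatment-related SAEs. No SAE route is described for non-fatal events from research procedures either. Death is the only event in section 16 with its own study form, so deleting the sentence alone would achieve nothing.
- *That site death forms would bias the mortality outcomes, being more complete for men under continuing cancer care.* The documents do not support this. Section 4 says: "Although there are no further planned study visits all men will be consented for healthcare data linkage to measure long-term outcomes". Mortality is among those outcomes, and nothing says that site forms feed the analysis.

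The reply does not remove the contradiction between 16.2 and 3.1.2, or the absence of a relatedness step. Reporting rules of this kind belong in the protocol and are not something commonly left to a SAP.

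**Conclusion.** The point holds in a limited form. The reason in 16.2 is wrong on the protocol's own definitions for every death that is not prostate cancer related. A death possibly related to the research cores or blood draw falls in that group, with no study-level notification or relatedness assessment defined for it. The same gap exists for serious non-fatal events from those procedures.

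The practical size is small in expected numbers and cannot be stated as a rate: few or none of the early deaths may be related to a research procedure. The point rests on the false premise, the gravity of the event if it occurs, and the low cost of correction. It should be changed, but it does not threaten the study's analyses. The conclusion assumes that neither the death form nor the monitoring plan already fills the gap; neither is shown.

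**What to change.** Amend section 16.2 along these lines:

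> *Prostate cancer related death is part of the longitudinal primary outcome and is recorded on the death form, not as an SAE. Any other death known to the site by the end of the 4-8 week record follow-up is notified promptly to the CI and sponsor on the death form, with the PI's statement of whether it may be related to the research cores or the research blood draw.*

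Three points go with it:

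- Keep this separate from the protocol-violation route of section 17, which is defined for breaches.
- Reconcile the opening of section 16 with 16.1 and 16.2, so that serious non-fatal events possibly related to the research cores or blood draw follow the same route.
- Say how other deaths after the 4-8 week window are handled, so that none is left unclassified. Section 4 already has mortality measured by linkage.

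The cost is a wording amendment, possibly one added field on the death form, and a few extra reports: for deaths, about 0 to 3 over the whole study under the assumption above. Non-fatal reports cannot be counted from the documents. No visits are added and no outcome definition changes.
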